# 9. RATIONALE

Meeting reproductive health (RH) needs for women living with HIV (WLWH) is critical to reduce unintended pregnancies and avert adverse maternal and child health (MCH) outcomes, including prevention of mother-to-child HIV transmission (PMTCT). Helping WLWH plan healthy pregnancies is also essential to ensure reproductive justice for this population. In a 2016 national survey in Kenya, we found **integrating RH counseling and service delivery into HIV care** resulted in increased contraceptive use ([1](#_ENREF_1)), consistent with other studies.([2-4](#_ENREF_2)) Yet, **implementation of high quality, women-centered RH services is challenging for HIV providers and health systems who** **lack time, skills, resources, and training.**([5-7](#_ENREF_5)) Tools and “apps” have been developed to facilitate general RH counseling and streamline services, but most lack rigorous evaluation and none have been designed to address unique RH needs and longer term support of WLWH in resource-limited settings.([8](#_ENREF_8), [9](#_ENREF_9))

While contraceptive initiation is high among WLWH, **30-50% discontinue within 1 year** in sub-Saharan Africa.([7](#_ENREF_7)) Counseling interventions can help mitigate circumstances that lead to discontinuation, a key driver of unmet need for family planning (FP).([10-12](#_ENREF_10)) In addition, **WLWH face** **unique HIV-related issues in reproductive life planning and supporting contraceptive decision-making and management beyond method initiation.** These include choice of antiretroviral treatment (ART) regimen (dolutegravir considerations), drug-drug interactions, side effects, safe conception (viral suppression and protecting serodiscordant partners), and provider and internalized stigma. Interventions to improve counseling and support for fertility planning and contraceptive continuation, tailored for WLWH, will help women make informed decisions to plan, space, or limit pregnancies; better achieve their RH goals; and optimize health outcomes.

# 10. HYPOTHESIS & STUDY QUESTIONS:

Our overarching hypothesis is that Mobile WACh Empower, a theoretically grounded counseling tool and two-way SMS intervention that connects WLWH with healthcare workers will improve women’s knowledge, skills and motivation to plan, space or limit pregnancy and achieve better RH goals and health outcomes.

# 11. OBJECTIVES

# *11.1 Broad Objectives*

Our overarching aim is to determine the effect of Mobile WACh Empower on reproductive health outcomes and to understand appropriate pathway to scale for this intervention.

## 11.2 Specific Objectives

We will leverage our team’s extensive, interdisciplinary experience on HIV, RH, and mobile health (mHealth) to implement and evaluate the Mobile WACh Empower intervention in a cluster randomized controlled trial (RCT) in the following aims:

**Aim 1:** To determine the effect of the Mobile WACh Empower intervention (counseling and SMS support) on contraceptive discontinuation rates. Secondary outcomes include dual method use and unmet need for FP.

Approach: We will conduct a cluster RCT of Mobile WACh Empower versus the standard of care (SOC) among WLWH seeking HIV care in 10 facilities in Nairobi and western Kenya followed for 2 years.

*Hypothesis: Women in the intervention arm will have lower contraceptive discontinuation rates and unmet need, and higher dual method use at 2 years compared to the SOC arm.*

**Aim 2:** To evaluate acceptability, appropriateness, feasibility, and scalability of Mobile WACh Empower implementation under real-world conditions.

Approach: We will conduct in-depth interviews and focus group discussions (FGDs) at intervention sites with a subset of WLWH enrolled in Aim 1 and site HIV care providers during the trial and at exit. FGDs with WLWH during the trial and at exit will be grounded in behavioral theory (Information-Motivation-Behavior Skills Theory) to determine patient-level intervention acceptability and feasibility. During the trial, IDIs will be conducted with providers as well as FGDs at exit. These will be grounded in implementation science (Consolidated Framework for Implementation Research) to understand health system-level acceptability, appropriateness, feasibility and plan for scalability.

*Hypothesis: The intervention will support women’s fertility and contraceptive choices, improve RH self-efficacy, meet needs for RH counseling and support, and streamline provider workflow and counseling. Readiness and implementation climate needed for scaling Mobile WACh Empower will also be assessed.*

**Aim 3:** To estimate the cost and cost-effectiveness of implementing Mobile WACh Empower in HIV clinics in Kenya on unintended pregnancies and MTCT. Approach: We will conduct micro-costing and time-motion observations to estimate intervention costs from a health system perspective. We will combine costs and trial outcome data from Aim 1 in a mathematical model to project the health and economic impact of implementing Mobile WACh Empower in Kenya, including costs per unintended pregnancy and MTCT averted.

*Hypothesis:* *Mobile WACh Empower will be a cost-effective approach for preventing unintended pregnancies.*

# 12. METHODOLOGY

Each AIM will have a separate Methodology section

## AIM 1: Mobile WACh EMPOWER RCT

## 12.1 Study Design

The study is a non-blinded cluster randomized controlled trial.

We will conduct a cluster RCT to evaluate a combined counseling intervention (tablet decision-support tool plus SMS for follow-up support) to (counseling and SMS support) on contraceptive discontinuation rates. Cluster RCTs are well-suited to interventions that occur at the clinic, rather than individual level. The randomization at a clinic level allows for the traditional benefits of randomization. We will include a total of 10 clinics in the RCT, 5 receiving standard of care and 5 receiving the intervention and compare contraceptive discontinuation as a primary outcome, and dual method use and unmet need for family planning as secondary outcomes, between the 2 arms.

Randomization procedures:

For the RCT, 10 clinics will be randomized to receive the Mobile WACh Empower intervention or no intervention (SOC). Depending on the heterogeneity of baseline facility factors, restricted randomization may be used to ensure an equal distribution of potentially confounding factors. [name] (Biostatistician) will generate the randomization assignment for each clinic.

Masking procedures: Because this is a clinic-level intervention, there will be no masking procedures.

Detailed Description of Procedures:

5 clinics will be randomized to receive the Mobile WACh Empower intervention and 5 to receive no intervention. Depending on the heterogeneity of baseline facility factors, restricted randomization may be used to ensure an equal distribution of potentially confounding factors such as urban vs. rural site or clinic size. [name] (Biostatistician) will generate the randomization assignment.

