## 12.2 Study Area Description

**Study sites**: The proposed study will be conducted at 10 HIV clinics in western Kenya and Nairobi county. We will select facilities from Bondo sub-County, Lumumba sub-Country, Rachuonyo District, Siaya District, Kisumu District General Hospitals in Western Kenya and Mathare North Health Center, Riruta Health Center, KNH, Kangemi Health Centre, Kibera South Health Center, Dandora 2 Health Centre, Kayole 2 Health Centre and Kariobangi North Health Centre. These facilities represent a mix of rural and urban facilities, all with sufficient patient volume to assure feasibility of recruitment.

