**12.5 Statistical analysis** We will compare facility and individual characteristics (accounting for clustering) to determine adequacy of randomization. In the primary intent-to-treat analysis, we will compare time to FP discontinuation (no method use for >1 month, 2 years of follow-up) using Cox-proportional hazards regression, accounting for clustering.([87](#_ENREF_87)) Women not initially on FP at baseline will enter the analysis once initiating FP. We will use Poisson generalized linear models (GLMs) with a log-link function to compare secondary outcomes, an offset of time and robust standard errors to compare rates of dual method use and unmet need for FP between arms accounting for clustering (Table 4). This analytical approach is appropriate for rare outcomes.([88](#_ENREF_88), [89](#_ENREF_89)) We will conduct an exploratory analysis comparing VL suppression (<1000 copies/mL) between arms among women who become pregnant using generalized estimating equations with a log link, exchangeable correlation structure, and clustering by clinic. Additional exploratory analysis comparing unintended pregnancy rates between arms will be done using a Poisson GLM as described above. Data will be disaggregated by age, marital status, fertility plans, FP method and user type (initiator, continuer, or switcher). Although we expect low attrition and no differences in attrition by arms we will assess whether there is selection bias due to attrition by comparing women retained vs. not retained and report any differences. We will use multivariate imputation by chained equations to impute variables with >25% missing values.

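### Restricted randomisation of the 10 clinics is optional, so an avoidable regional imbalance is allowed: with 5 western and 5 Nairobi clinics, a 20.6% chance of a 4:1 or worse split

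*Protocol*

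**What the plan says.** Section 12.1 (Study Design) fixes the allocation: "5 clinics will be randomized to receive the Mobile WACh Empower intervention and 5 to receive no intervention". On balance it says, once under the randomisation procedures and again in the detailed description, that "Depending on the heterogeneity of baseline facility factors, restricted randomization may be used to ensure an equal distribution of potentially confounding factors". The detailed description adds two examples, urban or rural location and clinic size: "restricted randomization may be used to ensure an equal distribution of potentially confounding factors such as urban vs. rural site or clinic size". Region is not among them. No degree of heterogeneity that would trigger restriction is given, and no factor is committed to.

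Section 12.2 (Study Area Description) says that "The proposed study will be conducted at 10 HIV clinics in western Kenya and Nairobi county". It names five western facilities ("Bondo sub-County, Lumumba sub-Country, Rachuonyo District, Siaya District, Kisumu District General Hospitals in Western Kenya") and eight in Nairobi, 13 candidates for 10 places, and adds: "These facilities represent a mix of rural and urban facilities, all with sufficient patient volume to assure feasibility of recruitment".

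Section 12.5 (Statistical analysis) compares time to discontinuation "using Cox-proportional hazards regression, accounting for clustering". It states no region term. It also plans to compare facility characteristics to judge whether randomisation worked, but names no action if it did not.

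**The concern.** With 10 units, chance alone often leaves a strong clinic-level factor unbalanced, and the sponsor gets one draw. Restriction depends on heterogeneity being found, yet section 12.2 already describes it: two regions and a rural and urban mix. An unrestricted draw would still follow the protocol. Restricting only on the two example factors would not necessarily balance region.

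Allocation is settled before enrolment, so a statistical analysis plan can adjust for a lopsided draw but cannot undo it. At stake are the primary contrast and both secondary contrasts. In an uneven draw, part of any regional difference enters the unadjusted arm difference. Even in an even draw, regional variation stays in the error term unless the model removes it. Section 16 (Study Limitations) expects structural barriers to be equally distributed by arm, and an unrestricted draw of 10 clinics does not secure that.

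**Working it through.** **Inputs from the protocol.** 10 clinics, 5 per arm (12.1). Two-sided α = 0.05, 80% power, coefficient of variation (CV) 0.2, 300 women per clinic with up to 10% attrition, discontinuation 50% against 30% (12.4). 300 less 10% gives m = 270.

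**Assumptions, not in the protocol.** 5 western and 5 Nairobi clinics. This follows if all five named western sites are used, and it matches the split given for the formative workshop clinics (12.1.i), but nothing fixes it for the trial. Region is taken to explain 25% or 50% of between-clinic variance.

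**1. The plan's own figure.** Unmatched cluster formula, clinics per arm:

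c = 1 + (1.960 + 0.842)² × [p0(1−p0)/m + p1(1−p1)/m + CV²(p0² + p1²)] / (p0 − p1)²

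= 1 + 7.849 × [0.25/270 + 0.21/270 + 0.04 × (0.25 + 0.09)] / 0.04 = 1 + 7.849 × 0.01530 / 0.04 ≈ 4.003

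Rounded up, this is 5 per arm, or 10 clinics, as in Table 3. Because c only just exceeds 4, five clinics per arm give about 90% power by the same formula.

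**2. Chance of regional imbalance.** An unrestricted 5:5 draw has C(10,5) = 252 equally likely allocations.

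- 4:1 either way: 2 × C(5,4) × C(5,1) = 50
- 5:0 either way: 2
- 4:1 or worse: 52/252 = 20.6%; 5:0 alone: 2/252 = 0.8%

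For other mixes that the 13 sites allow, the chance that one arm holds all the western clinics is:

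- 4 western and 6 Nairobi: 12/252 = 4.8%
- 3 and 7: 42/252 = 16.7%
- 2 and 8: 112/252 = 44.4%

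**3. Effect of a 4:1 draw.** The between-clinic SD in control is 0.2 × 50% = 10 points. With two equal regions the regional gap is 2 × 10 × √share, which is 10 points at 25% and 14.1 points at 50%. A 4:1 draw moves the unadjusted arm difference by (4/5 − 1/5) × gap = 6.0 or 8.5 points if there is no treatment effect. Under the planned 40% reduction the gap shrinks to 0.6 of its size in the intervention arm, so the shift is 0.3 × (1 + 0.6) × gap = 4.8 or 6.8 points, against a 20-point target.

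**4. Power and type I error.** Simulation with 20,000 runs per cell and m = 270, using a cluster-level t-test on clinic proportions as a stand-in for the clustered Cox model. Read the results to within about a point.

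| Allocation and analysis | Power, region 25% | Power, region 50% |
|---|---|---|
| Unrestricted, no region term | 87-88% | 87-88% |
| Stratified by region, no region term | 88-89% | 89% |
| Unrestricted, region term (5:0 counted as failure) | 89% | 95% |
| Stratified by region, region term | 92% | 98% |

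Type I error for the unrestricted, unadjusted test is about 5% averaged over draws. Given that a 4:1 draw has occurred, it is about 10.6% (25% share) or 17.0% (50% share). With a region term it returns to about 5%.

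If region explains nothing, stratifying and fitting region costs about 2 to 3 points of power.

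**The case against.** The protocol raises restriction twice, names candidate factors and gives the task to the biostatistician. Since its own site description shows heterogeneity, its condition arguably points towards restriction. The exact scheme may sit in a randomisation plan, and a region term in a statistical analysis plan, neither of which is at hand. Regional variance is also part of the CV of 0.2 behind Table 3, so it is budgeted for rather than overlooked.

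Much of this stands. The protocol neither chooses unrestricted randomisation nor rules out adjustment; it permits the weaker course. The absence of a region term alone would not be a finding. What remains is that the protocol leaves the allocation open, and no later document can change the draw once it is made.

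A reader might infer more than the documents support:

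- That the protocol contrasts rural western Kenya with urban Nairobi. It says only that the facilities mix rural and urban, and does not map this onto region.
- That region cannot be separated from arm after a lopsided draw. That is true only at 5:0. In the other 50 of the 52 allocations a region term can be fitted.
- That stratification itself yields the power gain. Alone it adds 1-2 points; most of the gain comes from the region term.

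**Conclusion.** The point holds as an avoidable chance-imbalance and efficiency problem. The protocol allows an unrestricted 5:5 draw of 10 clinics from two regions. If the mix is 5 and 5, the chance of a 4:1 or worse split is 20.6%. That figure should not be quoted without its condition, because other mixes give different values.

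It is not a validity failure. Average type I error is about 5%, and unrestricted, unadjusted power of about 87-88% is above the planned 80%. The higher error rates apply only given a 4:1 draw, no adjustment and a real regional gap. The power gain to about 92% or 98% rests on the assumed 25% or 50% variance share, for which the protocol gives no figure. The change is worth making because it costs little and cannot be made after allocation.

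**What to change.** In section 12.1, change *may* to *will* in both places and name region (Nairobi or western Kenya) as the factor. Randomise within region. With 5 and 5 clinics, fix a 3:2 and 2:3 split. If site selection is still open, an even number per region, such as 6 Nairobi and 4 western, allows exact balance. Clinic volume can be added through covariate-constrained randomisation if wanted.

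In section 12.5, include region in the primary model, so that the analysis matches the allocation and takes up most of the available gain.

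The cost is a few lines of text, some allocation code and one cluster-level degree of freedom. No extra clinics or women are needed.

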## 12.2 Study Area Description

**Study sites**: The proposed study will be conducted at 10 HIV clinics in western Kenya and Nairobi county. We will select facilities from Bondo sub-County, Lumumba sub-Country, Rachuonyo District, Siaya District, Kisumu District General Hospitals in Western Kenya and Mathare North Health Center, Riruta Health Center, KNH, Kangemi Health Centre, Kibera South Health Center, Dandora 2 Health Centre, Kayole 2 Health Centre and Kariobangi North Health Centre. These facilities represent a mix of rural and urban facilities, all with sufficient patient volume to assure feasibility of recruitment.

## 12.3 Study Population

**Box 2. Eligibility Criteria for WLWH**

- HIV-infected
- Receiving HIV care at study site
- Reproductive age (18-45; 14-17 if emancipated minors)
- Daily access to mobile phone (own phone or shared) with Safaricom SIM
- Plan to receive HIV care at enrollment facility for 2 years
- Speak English, Kiswahili, or Luo
- Literate or comfortable with someone reading study SMS

We will recruit WLWH and HIV providers receiving or providing HIV care, respectively, from 10 HIV clinics. These facilities will include Bondo sub-County, Lumumba sub-Country, Rachuonyo District, Siaya District, and Kisumu District General Hospitals in western Kenya and Mathare North Health Center, Riruta Health Center, KNH, Kangemi Health Centre, Kibera South Health centre, Dandora 2 Health Centre, Kayole 2 Health Centre, Kariobangi North Health Centre in Nairobi. Eligibility criteria are shown in **Box 2**. Adolescents age 14-17 with prior pregnancies are emancipated minors by Kenyan law. Literacy in study regions is high (>90%), but if women have a partner or family member whom they would feel comfortable having read them SMS no exclusions based on literacy will be made to enhance generalizability. This approach has been successful in prior Mobile WACh studies, including WLWH. Currently pregnant women will be excluded; breastfeeding women will be eligible.

## 12.4 Sample Size Determination

| **Table 3. Number of clusters needed assuming n=300 women per cluster (accounting for up to 10% attrition) 80% power, α=0.05, two-sided testing, coefficient of variation=0.2** | | | | | |
| --- | --- | --- | --- | --- | --- |
| *FP discontinuation* ***Arm 1*** | | | | | |
| **Arm 2** | **20%** | **25%** | **30%** | **35%** | **40%** |
| **45%** | 6 | 8 | 12 | 26 | 103 |
| **50%** | 6 | 6 | 10 | 14 | 32 |
| **55%** | 4 | 6 | 8 | 10 | 18 |
| **60%** | 4 | 6 | 6 | 8 | 12 |

Based on literature ([7](#_ENREF_7)) and recent data among women receiving HIV care in Kenya ([63](#_ENREF_63)) we anticipate 50% of women in the control arm will discontinue FP by 2 years. Assuming α=0.05, 2-sided testing, and a coefficient of variation of 0.2, 10 clinics (5 per arm), and 300 women/clinic we have 80% power to detect a 40% reduction in discontinuation for reasons other than planned pregnancy (30% discontinuation rate) (**Table 3**). Prior data suggest the coefficient of variation falls as cluster size increases, is often ≤0.25, but rarely >0.5; therefore, a coefficient of variation of 0.2 is expected to be adequate. We will enroll 347 women to allow for 10% attrition after enrollment plus additional attrition between consenting and the return visit for use of the counseling tool and completion of enrollment, for a total sample size for analysis of 3300 women. Power was conservatively calculated factoring in potential attrition. With 10 clusters we will also have sufficient power to detect a difference in unmet need for FP (reduction from 25% to 15%) and an increase in dual method use from 40% to 65%.

**12.5 Statistical analysis** We will compare facility and individual characteristics (accounting for clustering) to determine adequacy of randomization. In the primary intent-to-treat analysis, we will compare time to FP discontinuation (no method use for >1 month, 2 years of follow-up) using Cox-proportional hazards regression, accounting for clustering.([87](#_ENREF_87)) Women not initially on FP at baseline will enter the analysis once initiating FP. We will use Poisson generalized linear models (GLMs) with a log-link function to compare secondary outcomes, an offset of time and robust standard errors to compare rates of dual method use and unmet need for FP between arms accounting for clustering (Table 4). This analytical approach is appropriate for rare outcomes.([88](#_ENREF_88), [89](#_ENREF_89)) We will conduct an exploratory analysis comparing VL suppression (<1000 copies/mL) between arms among women who become pregnant using generalized estimating equations with a log link, exchangeable correlation structure, and clustering by clinic. Additional exploratory analysis comparing unintended pregnancy rates between arms will be done using a Poisson GLM as described above. Data will be disaggregated by age, marital status, fertility plans, FP method and user type (initiator, continuer, or switcher). Although we expect low attrition and no differences in attrition by arms we will assess whether there is selection bias due to attrition by comparing women retained vs. not retained and report any differences. We will use multivariate imputation by chained equations to impute variables with >25% missing values.

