**A well-designed, patient-centered, rigorously evaluated RH counseling intervention will not only address critical RH needs of WLWH but could add efficiency and decrease, rather than add to, provider and health system burden** and ultimately improve RH outcomes. Trials of counseling tools in other fields suggest they are superior to usual care in improving knowledge and setting realistic expectations of benefits and harms, reducing passivity in decision-making, and lowering decisional conflict.([52](#_ENREF_52)) They have also increased satisfaction with FP counseling.([53](#_ENREF_53)) However, current interventions focus on information aggregation and dissemination and fail to fully meet needs of individual patients or achieve sustained behavior change. **WLWH and the providers who care for them need a rigorously designed and evaluated patient-centered mHealth solution that provides holistic and integrated HIV/RH counseling and support for long-term outcomes. We propose to leverage our mHealth experience, and develop and test the Mobile WACh Empower intervention**, to integrate the values, preferences and individual reproductive plans of women by providing tailored counseling and decision-support (FP-related example **Figure 2**) to achieve long-term contraceptive adherence, switching, or discontinuation for pregnancy. Initial counseling in the clinic will focus on these individual domains, and we anticipate the intervention may indirectly result in task-shifting of counseling, alleviating some provider burden to offer comprehensive RH counseling. The intervention will simultaneously streamline and systematize counseling, reducing variation and counseling time on unacceptable or inappropriate FP methods, and improving patient tracking of RH indicators.

Estimating program costs and projecting cost-effectiveness of implementing Mobile WACh Empower can provide important information to decision makers in Kenya when allocating health budgets and deciding which interventions to implement. Mathematical modeling synthesizes costs and intermediate outcomes from trials to project long-term health outcomes of HIV interventions contextualized to local epidemics.([54](#_ENREF_54)) Costing and cost-effectiveness analyses (CEAs) are increasingly used to inform policy decisions and ensure efficient use of limited budgets to maximize population health.

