**Table 4. cRCT outcomes**

| **Outcome** | **Outcome type** | **Indicator** | **Source** | **Timing of assessment** | **Statistical Analysis** |
| --- | --- | --- | --- | --- | --- |
| **Aim 1** | | | | | |
| FP discontinuation | Primary | No FP used at exit (among FP users who desire pregnancy prevention) | Survey, clinic records | Quarterly, by 2 years | Cox proportional hazards, time to first event |
| Uptake of dual methods | Secondary | Using condoms and another modern FP method | Survey, clinic records | Quarterly, by 2 years | Poisson GLM (log-link with robust SE |
| Unmet need for FP | Secondary | Desire for pregnancy prevention but not using FP | Survey, clinic records | Quarterly, at 2 years | Poisson GLM (log-link with robust SE) |
| VL suppression at conception | Exploratory/  modeled | VL<1000 copies/mL among women planning pregnancy/pregnant | Lab results | First clinic visit when pregnant/planning pregnancy | Poisson GLM (log-link with robust SE) |
| Unintended pregnancy | Exploratory/  modeled | Pregnancy among women not intending pregnancy (excludes ambivalence) | Survey, clinic records, model | By 2 years | Poisson GEE (log-link with robust SE) |

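### The primary event is defined differently in 12.4, 12.5 and Table 4, and the analysis wording in 12.5 omits the planned-pregnancy exclusion on which the trial is powered

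*Protocol*

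**What the plan says.** Three places in the protocol define the primary outcome.

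- **Section 12.4 (sample size).** The control rate is given without reference to the reason for stopping: "we anticipate 50% of women in the control arm will discontinue FP by 2 years". The effect to be detected is qualified: "80% power to detect a 40% reduction in discontinuation for reasons other than planned pregnancy (30% discontinuation rate").
- **Section 12.5 (analysis).** The primary intent-to-treat comparison is of "time to FP discontinuation (no method use for >1 month, 2 years of follow-up"), by Cox regression accounting for clustering. It gives no reason criterion, and no censoring or competing-event rule for women who stop to conceive.
- **Table 4 (outcomes).** The primary indicator is "No FP used at exit (among FP users who desire pregnancy prevention"). The same row lists quarterly assessment and a Cox model for time to first event.

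The aim of the intervention matters here. Section 8 says that its tailored counselling should help women "achieve long-term contraceptive adherence, switching, or discontinuation for pregnancy". The conceptual framework (Figure 3) names the target behaviour as stopping contraception without a plan.

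**The concern.** The three versions differ on two points. The first is the event: a gap of more than one month at any time in 12.5, against status at exit in Table 4. A woman with a two-month gap who is back on a method at exit has the event under 12.5 but not under Table 4. The second is stopping for a planned pregnancy: excluded in 12.4, not mentioned in 12.5, and handled in Table 4 by restricting the population.

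Section 12.5 is the text an analyst would follow, and it lacks the exclusion. Taken at its word, it scores as a failure a woman who stops contraception to conceive as she planned, which the intervention is meant to support. The estimate would then describe all-cause stopping, with a ratio closer to 1 than the one the trial was sized to detect. In an unblinded trial, leaving several versions of the primary event in the protocol also leaves the choice between them open after data have been seen.

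**Working it through.** **Inputs from the protocol.** Two-sided α of 0.05, coefficient of variation k = 0.2, 5 clinics per arm and 300 women per clinic (12.4); 50% against 30% (12.4); 10 pregnancies per 100 person-years, planned share not given (Study Limitations). Table 3 is headed "Number of clusters needed assuming n=300 women per cluster (accounting for up to 10% attrition) 80% power, α=0.05, two-sided testing, coefficient of variation=0.2", so I take m = 300 × 0.9 = 270.

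**Reproducing the plan's figure.** The unmatched cluster formula for two proportions is

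c = 1 + (1.960 + 0.842)² × V / (p0 − p1)², with V = p0(1 − p0)/m + p1(1 − p1)/m + k²(p0² + p1²).

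For 50% against 30%:

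- V = 0.25/270 + 0.21/270 + 0.04 × 0.34 = 0.000926 + 0.000778 + 0.013600 = 0.015304
- c = 1 + 7.849 × 0.015304 / 0.04 = 4.003, rounded up to 5 per arm, or 10 clinics, as stated.

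With m = 300, c = 3.97, which would give 8 clinics. At m = 270 the formula matches 19 of the 20 cells of Table 3; the exception is 45% against 40% (103 stated, 106 computed).

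Because 4.003 is rounded up to 5, the design has more than 80% power. Power = Φ(|p0 − p1| × √(4/V) − 1.960) = Φ(3.233 − 1.960) = 0.90.

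**Adding planned-pregnancy stops, as 12.5 read literally would.** Take 50% and 30% as the 2-year risks of stopping for other reasons. The hazards are −ln(0.5)/2 = 0.3466 and −ln(0.7)/2 = 0.1783 per year, a ratio of 0.515. Add a planned-stop hazard g, equal in both arms. The total 2-year risk is 1 − exp(−2(h + g)). The values of g are assumptions.

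| g per 100 person-years | Control | Intervention | Hazard ratio | V | Power |
|---|---|---|---|---|---|
| 0 | 50.0% | 30.0% | 0.51 | 0.0153 | 0.90 |
| 3 | 52.9% | 34.1% | 0.55 | 0.0176 | 0.81 |
| 3.3 | 53.2% | 34.5% | 0.56 | 0.0178 | 0.80 |
| 5 | 54.8% | 36.7% | 0.58 | 0.0191 | 0.74 |
| 10 | 59.1% | 42.7% | 0.62 | 0.0230 | 0.58 |

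The last row treats every pregnancy at the protocol's rate as planned and so marks the far end of the range. At g = 5, c = 5.59, so 12 clinics would be needed for 80%. The 80% line is crossed at about g = 3.3, a 2-year planned-stop probability of 1 − exp(−0.066) = 6.4%.

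**Sensitivity to the method.** A noncentral t calculation on 8 degrees of freedom, with noncentrality |p0 − p1| × √(5/V), gives 0.88, 0.79 and 0.73 at g = 0, 3 and 5, and crosses 80% near g = 2.8.

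**Sensitivity to the meaning of 50%.** Suppose the control rate is all-cause, a share q of women stop for a planned pregnancy, and the 40% reduction applies only to the rest. The intervention risk is then (0.50 − q) × 0.6 + q. For q = 5% this is 32%, with power 0.80 to 0.82; for q = 10% it is 34%, with power 0.69 to 0.71. The conclusion is much the same.

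**The case against.** The strongest reply is that 12.5 does not say planned-pregnancy stops are failures. It gives a short parenthesis on the length of the gap and is silent on the reason. Wherever the protocol does address the reason (12.4, Table 4, the conceptual framework), it leaves planned stopping out, and Table 4's restriction to users who desire prevention is on its face close to the 12.4 endpoint. Desire is also to be captured quarterly for the unmet-need outcome, and competing-event detail often sits in an analysis plan, which is not at hand. This reply stands as far as intent goes. It does not remove the conflict between the three statements, which lies in the protocol's own wording.

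A reader might infer four stronger things that the documents do not support.

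- **That the trial loses its stated power.** Rounding up to 5 clinics per arm leaves a reserve. The loss depends on a planned-stop rate the protocol does not give, and its pregnancy rate is neither split by intention nor stated for contraceptive users.
- **That counting all stops biases the randomised comparison.** It does not. It changes the estimand and dilutes the ratio.
- **That Table 4 selects women on a post-randomisation desire measured at exit.** That is one possible reading. The exit wording attaches to method use, and the time at which desire is measured is left open.
- **That planned stops will be more frequent in the intervention arm.** This is plausible given the aim, but no figure supports any particular imbalance.

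**Conclusion.** The primary endpoint is stated inconsistently and needs to be reconciled before analysis. The exclusion that defines the powered endpoint is absent from the analysis section, and Table 4 adds an at-exit criterion that does not fit a time-to-first-event model.

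If 12.5 were applied literally, the target hazard ratio would move from 0.51 to 0.55 at 3 and 0.58 at 5 planned stops per 100 person-years, and power from about 0.90 to 0.81 and 0.74. The stated 80% holds up to roughly 3 per 100 person-years and fails beyond that.

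These figures rest on planned stopping being equal by arm and independent of other stopping, on the coefficient of variation staying at 0.2, and on a two-proportion approximation to the Cox analysis, which is also how the protocol sized the trial. The inconsistency itself rests on none of these assumptions.

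**What to change.** State one primary event, in the same words, in 12.4, 12.5 and Table 4: the first spell of more than one month without a method while not trying to conceive, using the fertility intention or reason for stopping recorded at the quarterly visit that covers the stop. Delete the at-exit wording from Table 4. Say in 12.4 whether the 50% control rate already excludes planned pregnancy.

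In 12.5, keep the planned clustered Cox model and censor stops for a planned pregnancy as a competing event, so that the model estimates a cause-specific hazard ratio. Report all-cause stopping as a sensitivity analysis.

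The cost is wording and, if the quarterly survey does not already have one, a reason-for-stopping item; the survey forms are not shown, so this cannot be checked. The drawback is that the reason is self-reported in an unblinded trial and could be reported differently by arm. The all-cause sensitivity analysis addresses this because it does not use the reason.
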